Disease-related malnutrition and dysphagia are associated with increased hospital morbidity and mortality, length of stay, readmission rates, and associated costs [22]. Nutritional screening, early detection, and monitoring of nutritional status and dysphagia should be a fundamental part of the care plan for patients, especially in patients aged 65 years and older in inpatient units [6,7]. However, research currently places insufficient emphasis on the coexistence of malnutrition and dysphagia at the hospital level. Indeed, in Spain, some studies address the nutritional status of people aged 65 years and older in various care settings, using different definitions and screening tools [1,4,16]. Despite this fact, there is a lack of national studies on the joint prevalence of malnutrition and dysphagia conducted on a large sample of patients and including an assessment of the risk factors associated with both processes, as well as their evolution and consequences during hospitalization.

Therefore, this project will study the evolution of nutritional status and dysphagia in patients aged 65 and over during the care process in medical and surgical hospitalization units in Spanish hospitals. In addition, sociodemographic, clinical, functional status, frailty, and healthcare context-related characteristics that may be associated with the presence of malnutrition and dysphagia will be identified. Finally, patient satisfaction with food services in the participating centers will be studied.

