### Variables and instruments

The study variables are organized into eight groups: i) Nutritional status; ii) Dysphagia; iii) Food quality and environment; iv) Socio-demographic variables; v) Clinical, functional, cognitive, and frailty variables; vi) Variables related to the risk profile; vii) Context variables; viii) Variables related to the care process.

Specifically, nutritional status and dysphagia are considered the main variables of the study. Likewise, the variables related to nutritional status are organized into:

Risk of malnutrition on admission: Malnutrition Universal Screening Tool (MUST) will be used to determine the risk of malnutrition. This questionnaire will measure current weight (kg), estimated weight three months ago (kg), height (cm), and Body Mass Index (BMI) (kg/m2). If height and weight cannot be measured or obtained, they will be estimated mid-upper arm circumference (MUAC) and calf circumference (CC) are set for weight and forearm length for height by the nutrition staff of each hospital. All patients included in the study will be assessed on admission, every 7 days, and at discharge.Diagnosis of malnutrition and degree of severity at admission: Global Leadership Initiative on Malnutrition (GLIM) criteria will be used for the population identified as high risk according to MUST. In addition, the following biochemical parameters will be collected: albumin, prealbumin CRP, CRP/prealbumin ratio, transferrin, total cholesterol, and the total number of lymphocytes. They will be collected on admission, every 7 days, and discharge provided that the minimum time for their re-determination has elapsed.Type of nutritional care established (according to risk and diagnosis of malnutrition): Includes aspects such as referral to the nutrition and dietetics unit, dietary adaptation according to alteration, nutritional supplementation, type of nutrition, or nutritional education. It will be recorded within 48 hours of admission, every 7 days and at discharge, and in case of any modification in the selected intervention, the starting date should be noted.Daily intake: a semi-quantitative questionnaire will be used to record the amount of intake made during the days of admission.

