#### Phase 1: Baseline situation

At the beginning of data collection, the facility manager will be responsible for recording the characteristics of the hospital nutrition unit and the hospital food service.

In the first 24–48 hours of admission, the nursing and nutrition staff will start collecting data related to functional variables (Barthel Index), clinical variables (diagnosis; renal or liver disease), cognitive variables (Pfeiffer questionnaire), frailty (polymedication; Frail questionnaire; Charlson index), risk profile (Braden scale; active infection), socio-demographic (Gijón scale), hospitalization and context (hospital; hospitalization unit), anthropometric parameters (height; weight; BMI), dysphagia-related variables (EAT-10; MECV-V) and malnutrition (biochemical profile; MUST; GLIM criteria).

Specifically, if the patient obtains a result ≥ 2 in the MUST questionnaire, the GLIM criteria will be applied by the nutritionists/endocrinologists to stratify the severity of malnutrition and the type of nutritional care will be adapted. On the other hand, if the patient obtains a result ≥ 3 in the EAT-10 questionnaire, an enter consultation with a speech therapist and endocrinologist or nutritionist will be requested for an in-depth assessment of the dysphagia with the MECV-V questionnaire and to adapt the nutritional care. In addition, the team of nutritionists at each centre will provide and explain to the patient or their companion the daily intake record booklet, which the patient or guardian must fill in during their hospital stay and which will be supervised in the morning shift by the nurse or nutritionists participating in the study. Similarly, within the first 24 hours of admission, the person responsible for the study in each hospital will contact the medical team to add the biochemical profiles (albumin, pre-albumin CRP, CRP/prealbumin ratio, transferrin, total cholesterol, and the total number of lymphocytes).

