### Data analysis

A descriptive analysis of all the study variables will be carried out, using the appropriate measures according to the type of variable and their corresponding 95% CIs. Firstly, depending on the groups to be compared and compliance with the application requirements, a bivariate analysis will be performed, including the chi-squared or Fisher’s exact test (qualitative variables) and Student’s t-test, ANOVA, Mann-Whitney U-test, or Kruskal-Wallis (quantitative variables), depending on the application conditions.

For the analysis of the evolution of the risk of malnutrition, McNemar’s test or Cochran’s Q test will be used for qualitative variables and paired t-test or Friedman’s rank test for quantitative variables. The incidence of risk of malnutrition and undernutrition will be calculated, as for dysphagia, during the care process and at patient discharge, estimating their corresponding Odds Ratios and 95% CI using logistic regression models.

To assess the possible risk factors for both malnutrition and dysphagia and the socio-demographic and clinical characteristics of the patients, multivariate logistic regression models will be constructed. As independent variables will include: type of nutritional care established according to the risk of malnutrition; daily intake; suspected and diagnosed dysphagia and days of stay. As control variables will include: those related to the risk profile; sociodemographic (sex, age); clinical, functional, cognitive and frailty variables. In the case of mortality and time to readmission, multivariate Cox regression models will be fitted. Independent variables will be included: level of risk of malnutrition at admission; diagnosis of malnutrition at admission; change in risk of malnutrition at admission, at 7 days and at discharge; change in nutritional status at admission, at 7 days and at discharge. Control variables will include: type of nutritional care established (according to risk of malnutrition); daily intake; contextual; related to risk profile; sociodemographic; clinical, functional, cognitive and frailty variables; suspected and diagnosed dysphagia. In all multivariate models, possible interaction effects and possible collinearity will be analyzed.

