This project will help to understand the different contexts of action, at the hospital level, and identify the variables that influence the development of malnutrition and dysphagia.

To propose the creation of future research that evaluated the effectiveness of screening and management of malnutrition and dysphagia and lead to the development of detection and intervention protocols for the management of both problems in the hospital setting. In this way, a new approach will be implemented in the planning of quality care for the patient/family, thus reducing the substitution of performance in clinical practice.

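### Care-context variables are promised as factors for malnutrition and dysphagia but are missing from the logistic model lists, so context gets no adjusted estimate

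*Protocol article*

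**What the plan says.** All places are in the protocol article.

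- **Introduction.** Context is one of the groups of candidate factors: "frailty, and healthcare context-related characteristics that may be associated with the presence of malnutrition and dysphagia will be identified". The Discussion repeats the ambition: "This project will help to understand the different contexts of action, at the hospital level, and identify the variables that influence the development of malnutrition".
- **Variables and instruments.** Context is a group of its own among the eight: "vi) Variables related to the risk profile; vii) Context variables; viii) Variables related to the care process".
- **Phase 1: Baseline situation.** Each patient's record includes "hospitalization and context (hospital; hospitalization unit". Separately, each site is responsible for "recording the characteristics of the hospital nutrition unit and the hospital food service".
- **Data analysis, logistic models for malnutrition and dysphagia.** The independent variables are "type of nutritional care established according to the risk of malnutrition; daily intake; suspected and diagnosed dysphagia and days of stay". The controls are given as: "As control variables will include: those related to the risk profile; sociodemographic (sex, age); clinical, functional, cognitive and frailty variables".
- **Data analysis, Cox models for mortality and readmission.** The control list in the same paragraph includes contextual variables, and it names the sociodemographic group without a restricting bracket.
- **Data analysis, mixed models.** Mixed logistic models are added, with unit and hospital as levels. Their stated purpose is to allow for correlation between patients in the same unit or hospital.

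**The concern.** Context is promised as a factor for malnutrition and dysphagia, and it is collected. It is then adjusted for in the models of mortality and readmission, but not listed in the models of the two outcomes for which it was promised. Two things are at stake.

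1. For the sociodemographic, clinical, functional and frailty groups named in the Introduction, the logistic lists provide a multivariable model. For context they do not.
2. Medical and surgical units are pooled. If malnutrition risk and a patient characteristic both differ between the two types of unit, leaving unit type out can shift the odds ratio of that characteristic.

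**Working it through.** **1. Comparison of the lists**

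| Variable group | Promised as factor (Introduction) | Logistic lists | Cox list |
|---|---|---|---|
| Clinical, functional, frailty | yes | yes | yes |
| Sociodemographic | yes | yes, with sex and age in brackets | yes, no bracket |
| Healthcare context | yes | **no** | yes |

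The article names covariate groups model by model, so the absence is a difference between two explicit lists in one paragraph.

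**2. What the mixed models supply.** A random intercept for unit or hospital yields a variance. An odds ratio for medical versus surgical unit, food service or nutrition unit appears only if that characteristic enters as a fixed effect, and none is listed.

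**3. Whether omission can bias other odds ratios.** The documents give no rates by unit type, so everything in this step is assumed and shows the mechanism only. The simulation used 9 hospitals with 6 units each and a unit standard deviation of 0.3 on the logit scale. A factor with true odds ratio 1.00 was present in 40–60% of medical and 30% of surgical patients, and the medical-versus-surgical odds ratio was 1.5–2.0. There were no other covariates and 20 runs per scenario.

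| Factor prevalence, medical / surgical | Unit-type OR | Single-level, no context | Random unit intercept | With medical/surgical term |
|---|---|---|---|---|
| 40% / 30% | 1.5 | 1.04 | 1.02 | 1.00 |
| 50% / 30% | 1.5 | 1.09 | 1.04 | 1.01 |
| 50% / 30% | 2.0 | 1.14 | 1.03 | 0.99 |
| 60% / 30% | 2.0 | 1.26 | 1.09 | 1.03 |

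On these assumptions the random intercept removes roughly half to three quarters of the shift. The fixed term brings the estimate to about 1. Adjustment for diagnosis, which is planned, is not in these figures and should reduce the shift further.

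**4. Whether the sample allows the extra terms.** Inputs from Sample/Participants: k = 20, rule n = 10(k + 1), losses 15%, 453 per hospital, 9 hospitals.

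- The plan's own figures reproduce. 10 × 21 = 210, and 210 × 1.15 = 241.5, rounded up to 242. For prevalence, 1.96² × 0.25 / 0.05² = 384.1, rounded up to 385; 385 / 0.85 = 452.9, rounded up to 453; 453 × 9 = 4077.
- Within one hospital, adding unit type gives k = 21. Then 10 × 22 = 220, and 220 / 0.85 = 258.8, rounded up to 259, below 453.
- In the pooled model, adding unit type and 8 hospital indicators gives k = 20 + 1 + 8 = 29. Then 10 × 30 = 300, and 300 / 0.85 = 352.9, rounded up to 353, far below 4077.

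The stated maximum of 20 predictors is exceeded only if all 20 places are already taken.

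**The case against.** The strongest reply is that little is missing. The formal objectives (Aims) speak only of associated factors; context is named in Introduction prose, which does not promise adjustment. Food service and nutrition unit appear in the fifth objective as things to determine, beside satisfaction. All variables are to be described with confidence intervals, bivariate tests are planned, and Sample/Participants announces an analysis by hospital, which removes confounding between hospitals. The controls include clinical variables, which Phase 1 defines to include diagnosis, a direct measure of case mix. The unit level of the mixed models absorbs much of any ward difference. Finally, a condensed article may leave exact covariates to an analysis plan.

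Most of this stands, and it rules out two stronger readings.

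- *A reader might infer that the aim goes unanswered.* It does not: descriptive, bivariate and by-hospital results on context remain. What is absent is an adjusted estimate.
- *A reader might infer that medical/surgical case mix does confound the reported factors, by a known amount.* The documents do not support that. A crude table with assumed rates (50/50 ward mix, malnutrition risk 40% and 20%, dependence 50% and 20%, no association within ward) gives OR = (0.12 × 0.47) / (0.23 × 0.18) = 1.36, with z = 4.0 at n = 385 × 9 = 3465. That table has no covariates and no unit effect, so it matches no planned model. With a random unit intercept added (2–6 units per hospital assumed), the mean odds ratio falls to 1.04–1.09. With milder rates (risk 35% and 25%) the crude odds ratio is 1.17 with z = 2.0, which reaches p<0.05 only about half the time.

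The reply does not remove the mismatch itself. The article does list covariate groups, and it lists context for one set of models and not the other. Analysis by hospital does not separate medical from surgical units within a hospital. The mixed models are additional to the single-level ones and, as described, estimate no context effect.

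The narrowing of the sociodemographic group to sex and age may be only an example. That the social-risk (Gijón) scale is excluded is an inference, so it is a question for the authors.

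**Conclusion.** The point holds as an internal mismatch with a limited consequence. A factor group that is promised and collected has no adjusted estimate for malnutrition or dysphagia, although it is a covariate in the Cox models. Residual medical/surgical confounding of the patient-level odds ratios is possible, most clearly in the single-level models, but its size cannot be given from the documents. The simulated figures rest on assumed rates and omit the planned clinical adjustment. Neither the sample size nor the validity of the descriptive results is affected. This is an inexpensive improvement to the analysis wording.

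**What to change.** - Add the contextual group to the logistic covariate list, as in the Cox list. Enter unit type (medical/surgical) as a fixed effect in both the single-level and the mixed logistic models, and report its adjusted odds ratio.
- Account for hospital once: either as the random level of the mixed model or as 8 indicators in the pooled single-level model.
- If the pooled model then exceeds 20 predictors, restate that maximum in Sample/Participants for the pooled analysis. The by-hospital models need at most the unit-type term.
- Report nutrition-unit and food-service characteristics descriptively, hospital by hospital. They take at most nine values, cannot be separated from hospital indicators, and should not be tested as if each patient were an independent observation of them.
- State whether the bracket after sociodemographic in the logistic list is meant to exclude the social-risk scale recorded in Phase 1.

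The cost is wording only. Hospital and unit are already recorded, and no extra patients are needed.

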## Materials and methods

### Research hypothesis

The nutritional status of patients aged 65 years and over admitted to the medical and surgical inpatient units of the participating hospitals evolves unfavourably from admission to discharge and may increase the length of stay, hospital mortality, and early readmission.

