### Aims

The main objective of this project is to assess the risk of malnutrition and nutritional status on admission and its evolution until discharge, in patients aged 65 and over admitted to medical and surgical units in hospitals of the Spanish National Health System. In addition, the aim is to respond to the following specific objectives:

To identify the incidence and prevalence of risk of malnutrition and the presence of malnutrition and associated factors on patient admission and discharge.To describe the evolution of nutritional status during patient hospitalization.To analyze the average length of stay, hospital mortality, and early readmission as a function of nutritional status at admission and the presence of dysphagia in the study cohort.To determine the incidence and prevalence of dysphagia and associated factors on admission and discharge.To determine satisfaction with the quality of patient nutrition at discharge, the type of hospital food service, and the characteristics of the hospital nutrition unit.

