#### Phase 2: Follow-up

Participants will be monitored every 7 days until they are discharged from the hospital. In this way, the researchers in charge will make a forecast of follow-up dates. In addition to the variables indicated, the nutritional care established will be adapted according to the evolution of the nutritional status and degree of dysphagia of the patient during their hospital stay, as part of the usual practice in each centre. On each occasion, a record will be kept of the person collecting the data.

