#### Phase 3: Situation on discharge

In addition to the variables indicated, on the day of discharge from the hospital, the daily intake record book will be collected and the food satisfaction survey will be provided. The variables related to the care process (days of stay, hospital mortality, and whether it was early readmission) will also be recorded.

Finally, the patient will be given the continuity of care report at discharge, drawn up by the responsible physician together with the nursing recommendations and information sheets on care related to malnutrition or dysphagia, as appropriate.

Data collection will be carried out electronically through Research Electronic Data Capture (REDCap) (www.prooject-redcap.org) [25,26]. This is a web application that allows the creation of electronic data notebooks for research projects and their online and offline collection from computers and other mobile devices. It also includes a scheduling and alarm system to manage data collection during monitoring. In this regard, it should be noted that the researchers who take on the data collection will receive training on the operation of REDCap and that a pilot of the process of recruiting participants and data collection will be carried out for one month.

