Additionally, multilevel models (generalized linear mixed models) with multivariate logistic link function will be implemented to account for possible correlation between patients admitted to the same medical or surgical units (first level) or hospital (second level).

In case of losses to follow-up, multiple imputation techniques will be used for missing data. In all cases, bilateral contrast will be used and will be considered significant when p<0.05. The analysis will be performed using SPSS v28.

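### The Cox model planned for hospital mortality in effect censors at live discharge, a competing event that malnutrition is expected to delay, so its hazard ratio can understate or miss a higher probability of dying in hospital.

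*Protocol article*

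**What the plan says.** The Data analysis section of the protocol article assigns a model to death and readmission together: "In the case of mortality and time to readmission, multivariate Cox regression models will be fitted". The predictors include "level of risk of malnutrition at admission; diagnosis of malnutrition at admission", followed by changes in risk and status during the stay.

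The death outcome is defined elsewhere as death in hospital:

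- Aims: "To analyze the average length of stay, hospital mortality, and early readmission as a function of nutritional status at admission" and by the presence of dysphagia.
- Research hypothesis: nutritional status worsens during the stay and "may increase the length of stay, hospital mortality, and early readmission".
- Phase 3 (situation on discharge): "The variables related to the care process (days of stay, hospital mortality, and whether it was early readmission) will also be recorded".

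The Phase 2 section sets the follow-up: "Participants will be monitored every 7 days until they are discharged from the hospital". No section describes a check of vital status after discharge. No section mentions competing events or cumulative incidence, or assigns a logistic model to hospital death. The logistic models in Data analysis are assigned to malnutrition and dysphagia. The multilevel logistic model at the end of that section is not tied to a named outcome. Multiple imputation is reserved for losses to follow-up, and live discharge is not a loss.

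**The concern.** If the event is death in hospital and time stops at discharge, an ordinary Cox model treats each patient discharged alive as censored on that day. Live discharge ends the possibility of the event and happens to those who recover. That makes it a competing event.

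This matters here because the protocol expects the exposure to act on both events. The hypothesis links poor nutritional status to longer stay as well as to death, and the Introduction gives the same background: "Disease-related malnutrition and dysphagia are associated with increased hospital morbidity and mortality, length of stay, readmission rates, and associated costs". A patient who stays longer is exposed to the risk of hospital death for more days. The proportion who die in hospital can then rise while the death rate per day in hospital rises less, or not at all. The Cox model reports only the daily rate. A reader of the results would probably take a hazard ratio near 1 to mean that hospital mortality does not depend on nutritional status at admission, and that could be wrong.

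**Working it through.** **What the documents give.** They contain no figure for hospital mortality, length of stay or a hazard ratio, so there is no planned figure on this point to reproduce. The sample size does reproduce and sets the scale: 1.96² × 0.5 × 0.5 / 0.05² = 384.1, rounded up to 385; 385 / 0.85 = 452.9, so 453 per hospital; 9 × 453 = 4077. It does not depend on this point. All hazards below are assumptions.

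**Formula.** Take constant daily hazards of death in hospital (d) and of live discharge (l). The probability that the stay ends in death is d / (d + l). The Cox hazard ratio with censoring at discharge is the ratio of the two d values and takes no account of l.

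**Same daily death hazard, slower discharge.** Set d = 0.004 per day in both groups and l = 1 / (mean time to live discharge).

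| Group | Mean time to live discharge | Hospital death risk | Risk ratio | Cox HR |
|---|---|---|---|---|
| Well nourished | 8 days | 0.004 / (0.004 + 1/8) = 3.10% | reference | reference |
| Malnourished | 10 days | 0.004 / (0.004 + 1/10) = 3.85% | 1.24 | 1.00 |
| Malnourished | 12 days | 0.004 / (0.004 + 1/12) = 4.58% | 1.48 | 1.00 |
| Malnourished | 14 days | 0.004 / (0.004 + 1/14) = 5.30% | 1.71 | 1.00 |

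**Sensitivity to baseline mortality.** Keep the daily death hazard equal, take a mean stay of 8 days in the reference group, and multiply the discharge hazard in the malnourished by 0.9 down to 0.5. The risk ratio runs from 1.11 to 1.94 at 3% baseline hospital mortality, from 1.11 to 1.91 at 5%, and from 1.10 to 1.82 at 10%. The Cox hazard ratio is 1.00 throughout. The gap therefore depends mainly on how much discharge is delayed and little on baseline mortality.

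**A harmful effect on both events.** With 5% baseline mortality and a mean stay of 8 days, d = 0.05 / 8 = 0.00625 and l = 0.95 / 8 = 0.11875. Let malnutrition multiply d by 1.3 and l by 0.8. The risk is 0.008125 / (0.008125 + 0.095) = 7.9%, a risk ratio of 1.58, against a Cox hazard ratio of 1.30. The direction is right but the size is understated.

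**Simulation at the study's scale.** Each run had 3465 evaluable patients (4077 × 0.85) and 30% malnourished (rounded from the 26.9% on admission cited in the Introduction). Baseline mortality was 5% and mean stay 8 days, with 100 runs per scenario and the planned two-sided 0.05 level.

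- Discharge hazard × 0.7, death hazard unchanged: the true risk is 7.0% against 5.0%. The Cox model censoring at discharge gave a hazard ratio of 1.03 and was significant in 6% of runs. A subdistribution model gave 1.46 and was significant in 73%.
- Discharge hazard × 0.8, death hazard × 1.3: the Cox model gave 1.29 (significant in 45%), the subdistribution model 1.57 (significant in 89%).

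With 100 runs, these percentages carry an error of up to about 10 points.

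**The case against.** The strongest reply is that the article states no censoring rule. It names a model family, and it condenses a fuller protocol in which the handling of live discharge may be set out. The Cox sentence says mortality without the word hospital, and the readmission half of it needs information from after discharge. It is true that censoring at discharge is inferred. However, the hypothesis, aims, data collection and conclusions all specify hospital mortality, and follow-up of readmission does not turn that outcome into death after discharge. The point concerns a stated model that does not match its stated objective, which is more than an unwritten detail.

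Second, the Cox estimate is a legitimate cause-specific hazard ratio and a standard target for risk-factor work. That also stands. The objective speaks of hospital mortality as a function of nutritional status without naming a measure, but its plain sense is how many die in hospital, and the Cox model alone does not answer that.

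Third, crude comparisons are planned. Hospital mortality is a recorded categorical variable, so chi-squared or Fisher tests would show the proportions who died, and length of stay by nutritional status is itself an objective. This lessens the concern, but these analyses are unadjusted. No adjusted analysis is assigned to the probability of hospital death.

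A reader might go further and infer that the Cox model would reverse the finding and make malnutrition look protective. That is arithmetically possible only if malnutrition lowers the daily hazard of death in hospital. Nothing in the documents suggests this, and the Introduction reports higher mortality. A reader might also worry about inflated Kaplan-Meier estimates, but no such curves are planned.

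**Conclusion.** The point holds as a mismatch between model and objective. As written, the only adjusted analysis assigned to hospital mortality estimates a daily rate of death among patients still in hospital, and the study's own hypothesis gives a reason why that rate and the probability of hospital death should diverge. The likely consequence is an understated or missed association. In the central illustration, a 48% higher risk of hospital death corresponds to a hazard ratio of 1.00, with a range of 24% to 71% for 10 to 14 days to live discharge.

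The size rests on assumed constant hazards and assumed times to discharge, because the documents give none. The mechanism needs two things: that poor nutritional status delays live discharge, as the protocol expects, and that patients discharged alive leave the risk set at discharge, as the outcome definition and follow-up imply. The Cox hazard ratio is not invalid, and an error is not certain to appear in the results. If discharge is not delayed, the two measures nearly agree.

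**What to change.** State that the adjusted analysis of hospital mortality is a logistic mixed model of died against discharged alive, with unit and hospital levels and nutritional status at admission as the exposure. The plan already names this model type, but it must be extended explicitly to this outcome. Days of stay should not be a covariate in it, since adjusting for stay would bring back the per-day comparison. Patients withdrawn on transfer have neither outcome recorded, so say how they are handled.

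If the Cox model is kept, label it cause-specific, state that live discharge is a competing event, and report it with the matching cause-specific model for live discharge and the cumulative incidence of death by nutritional status at admission.

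The cost is a change of analysis wording and a little extra analysis. Days of stay and hospital mortality are already recorded at discharge, and the sample size does not change. If cumulative incidence is reported, check that the planned software can produce it.
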